## Abstract

**Introduction:**

Genomic data constitute a valuable adjunct to routine surveillance that can guide programmatic decisions to reduce the burden of infectious diseases. However, genomic capacities remain low in Africa. This study aims to operationalise a functional malaria molecular surveillance system in Mozambique for guiding malaria control and elimination.

**Methods and analyses:**

This prospective surveillance study seeks to generate *Plasmodium falciparum* genetic data to (1) monitor molecular markers of drug resistance and deletions in rapid diagnostic test targets; (2) characterise transmission sources in low transmission settings and (3) quantify transmission levels and the effectiveness of antimalarial interventions. The study will take place across 19 districts in nine provinces (Maputo city, Maputo, Gaza, Inhambane, Niassa, Manica, Nampula, Zambézia and Sofala) which span a range of transmission strata, geographies and malaria intervention types. Dried blood spot samples and rapid diagnostic tests will be collected across the study districts in 2022 and 2023 through a combination of dense (all malaria clinical cases) and targeted (a selection of malaria clinical cases) sampling. Pregnant women attending their first antenatal care visit will also be included to assess their value for molecular surveillance. We will use a multiplex amplicon-based next-generation sequencing approach targeting informative single nucleotide polymorphisms, gene deletions and microhaplotypes. Genetic data will be incorporated into epidemiological and transmission models to identify the most informative relationship between genetic features, sources of malaria transmission and programmatic effectiveness of new malaria interventions. Strategic genomic information will be ultimately integrated into the national malaria information and surveillance system to improve the use of the genetic information for programmatic decision-making.

**Ethics and dissemination:**

The protocol was reviewed and approved by the institutional (CISM) and national ethics committees of Mozambique (Comité Nacional de Bioética para Saúde) and Spain (Hospital Clinic of Barcelona). Project results will be presented to all stakeholders and published in open-access journals.

**Trial registration number:**

NCT05306067.

Strengths and limitations of this studyNext-generation sequencing will be performed in country through the establishment of technical and computational infrastructure as well as analytical tools.The project builds from recent elimination experiences in southern Mozambique and uses a biorepository of already collected *Plasmodium falciparum* samples to select multiallelic short-range haplotypes (microhaplotypes) that increase the power of biallelic loci for phase inference in polygenomic infections.A joint epidemiological-genetic analysis will enable better predictions of the operational efficacy of new interventions.We will assess the value of a new surveillance system at antenatal visits to improve the programmatic performance of malaria control and elimination activities.More evidence on the association between malaria transmission intensity and genetic data is required for the use of malaria molecular surveillance data to assess the effectiveness of malaria interventions.

## Introduction

Pathogen genomics has the potential to transform the surveillance, prevention and control landscape of infectious diseases. The rapid innovation in sequencing technologies has led to the development of robust next-generation sequencing equipment with the ability for high pathogen resolution at increasingly affordable prices. This development has subsequently facilitated the incorporation of pathogen genomics in disease surveillance systems in high-income countries, allowing for targeted and effective control of disease threats through the timely and in-depth pathogen characterisation.^1^ Genomics-based surveillance is therefore becoming an integral strategy towards control and elimination of diseases such as COVID-19, tuberculosis, malaria, HIV and food-borne pathogens, among others.^2^

The strategic use of genetic variation in *Plasmodium falciparum* can boost the capacity of malaria control and elimination programmes to deploy the most efficient interventions.^3^ Molecular tools and use cases for decision making are currently being considered by the WHO which, through a technical consultation on the role of parasite and anopheline genetics in malaria surveillance,^4^ identified different levels of action based on evidences available. Genetic data can flag the emergence of mutations conferring resistance to antimalarials (ie, artemisinins)^5^ or deletions that affect rapid diagnostic test (RDT) sensitivity (ie, *P. falciparum histidine-rich protein 2* [*pfhrp2*]).^6–8^ Genomic scans for selection^9^ can identify other parasite adaptations mediated by single nucleotide polymorphisms (SNPs) and structural variations (gene copy number)^10^ that may require a programmatic response. Parasite-relatedness metrics such as identity by descent (IBD)^11^ can be used to characterise the key drives of ongoing transmission to identify foci^12 13^ and to discriminate between indigenous and imported cases in areas approaching elimination.^14–16^ Bottlenecks in parasite population driven by control and elimination efforts have been shown to reduce *P. falciparum* genetic diversity and increase similarity due to inbreeding and recent common ancestry.^17^ These evidences provide the basis for modelling efforts to recapitulate features of malaria transmission from genetic data and inform about the effectiveness of antimalarial interventions.^18–23^ However, further evidence is needed to demonstrate the feasibility and appropriateness of using genetic data as a proxy for transmission intensity and define the conditions under which that feasibility applies. Moreover, standardised approaches for detecting resistance through molecular markers are lacking, and variation in sample type, collection, storage, DNA extraction, marker detection and analysis of results can undermine the comparability of findings, as well as the sensitivity and specificity of methods used. Adequate genotyping methods, sampling frameworks, analytical pipelines and demonstration studies are still required across a range of malaria intensities, programmatic environments and use scenarios.

Strategic *P. falciparum* genetic information can be integrated into innovative cost-efficient surveillance approaches, such as those targeting pregnant women attending antenatal care (ANC) clinics.^24^ Women at ANC are a generally healthy, easy-access population, contributing valuable data for infectious disease surveillance (ie, HIV^25^ and syphilis^26^) and wider health metrics at the community level, including a proxy of the malaria burden in the community.^27–32^ Moreover, ANC-level malaria surveillance can provide a routine measure of the malaria burden in pregnancy, which countries lack, while potentially improving pregnancy outcomes by treating infections at first trimester. Women attending ANC also provide an attractive sampling population for measures of exposure to malaria beyond simply presence or absence of parasite infection. In particular, in addition to measuring complexity of infection or parasite flow-rates between populations, molecular analysis of *P. falciparum* samples collected from pregnant women may provide a means for the identification of adaptations developed by the parasite to control strategies, such as antimalarial resistance and deletions of antigens targeted by RDT that can compromise diagnosis, treatment and prevention.

Despite the potential benefits and the greater need to control the high burden of infectious diseases, genomic surveillance capacity remains low for many public health programmes in Africa.^2^ In order to reduce inequities in the access to sequencing technologies, this project aims to promote capacities in Mozambique for operationalising a functional malaria molecular surveillance (MMS) system for decision-making.^4^ Mozambique is among the 10 countries with the highest burden of malaria worldwide, with an estimated 10.8 million cases in 2020.^33^ However, malaria transmission is very heterogeneous in the country, with a high burden in the north and very low transmission in the south. Therefore, the project aims to address National Malaria Control Programme (NMCP) programmatic needs for elimination initiatives in southern Mozambique and burden reduction in the north (figure 1).

**Figure 1 F1:**
[figure not shown]
Malaria genomic use cases and National Malaria Control Programme (NMCP) decisions. The letter on the left (A–D) expresses the level of action described in the WHO Technical consultation on the role of parasite and anopheline genetics in malaria surveillance. (A) Immediate action; (B) medium-term action; (C) long-term action. Arrows in colour at the right express the research required for action in the medium-term and long-term (grey, not essential for action; green, immediate evidence; yellow, medium-term evidence). ANC, antenatal care clinics; IPT, intermittent preventive treatment; MDA, mass drug administration; rfMDA, reactive focal MDA; SMC, seasonal malaria chemoprevention.

## Methods and analysis

### Study design

This is a prospective genomic surveillance study of *P. falciparum* samples to be collected between 2022 and 2023 from a variety of transmission intensities and geographies in Mozambique to inform three use cases: appropriate malaria diagnostics and treatment; characterising transmission sources in low transmission settings and identifying intervention mixes with optimal effectiveness to reduce burden in moderate-to-high transmission areas. To achieve this, three different sampling approaches will be performed. First, all malaria cases will be sampled throughout the year in two low transmission districts of southern Mozambique currently targeted by reactive malaria surveillance activities (*dense sampling*). Second, a targeted approach will aim to collect a predefined number of samples at selected health facilities in the country. In low transmission settings, sampling will be conducted throughout the year, while two surveys will be conducted in medium-to-high transmission settings: one during the rainy and a second one during the dry season (which extend from November to April and May to October, respectively). During the high transmission (rainy) season, an LDH-based RDT will be added to the standard routine HRP2-based diagnostics to identify potential false negative results due to *pfhrp2/3* deletions among clinical cases.^34^ And third, *ANC sampling* of pregnant women at first attendance will be conducted throughout the year at selected health facilities in the country. The overarching sampling strategy for the study will however remain flexible and iterative, informed by sample analysis as the study progresses, and in view of future sampling and research activities being conducted by the Ministry of Health, National Institute of Health and other stakeholders in Mozambique, to avoid sampling overlap and ensure a diversity of sampled locations.

The project will also leverage from clinical trials and surveillance activities being conducted in Mozambique between 2021 and 2024, namely the Malaria Indicator Survey (2022–2023) in southern Mozambique; the therapeutic efficacy survey (2022) in sentinel sites in the country (Montepuez in Cabo Delgado, Moatize in Tete, Dondo in Sofala, Mopeia in Zambézia and Massinga in Inhambane);^35 36^ reactive surveillance activities in Magude and Matutuine (Maputo Province; 2022-2023); a phase III cluster-randomised, open-label, clinical trial in 2022 to study the safety and efficacy of ivermectin mass drug administration to reduce malaria transmission in Mopeia District (Zamb‘ézia Province); a large-scale implementation development project aiming at maximising the delivery and uptake of perennial malaria chemoprevention (formerly intermittent preventive treatment in infancy) in Massinga District (Inhambane Province; 2022–2024); a hybrid effectiveness-implementation study to evaluate the feasibility and effectiveness of seasonal malaria chemoprevention with sulfadoxine–pyrimethamine (SP) and amodiaquine inNampula Province (2022) and a programmatic delivery of a population-based mass drug administration with dihydroartemisinin-piperaquine in Manjacaze district (Gaza Province; 2022–2023).

### Study settings and participants

Nine provinces were identified through consultation with the NMCP for inclusion in the study: Maputo City, Maputo, Gaza, Inhambane, Niassa, Manica, Nampula, Zamb‘ézia and Sofala. Selection of study sites will be stratified by transmission intensity into two major strata: (a) low transmission (Maputo city and Maputo Province, where individual case notification is being implemented to reach interruption of transmission) and (b) medium-to-high transmission areas (Gaza, Inhambane, Niassa, Manica, Nampula, Zamb‘ézia and Sofala provinces, targeted by burden-reducing strategies). Overall, a total of 19 districts will be included, which provide a diverse range of epidemiological settings (see table 1 and figure 2).

**Table 1 T1:** Study provinces and districts targeted in the protocol

Transmission	Region	Province	District	Sampling			
				Dense	Targeted		Other sources
					HFS	ANC	
Low	South	Maputo City	Kamavota, KaMaxaqueni and Nlhamankulu		X*		
		Maputo Province	Boane and Manhiça		X*		
			Magude	X*		X†	React
			Matutuine	X*			React
Medium-to-high		Gaza	Manjacaze		X‡	X†	MDA-DP
		Inhambane	Maxixe		X‡	X†	
			Massinga		X‡	X†	PMC and TES
	Central	Manica	Guro and Gondala		X‡	X†	
		Sofala	Chemba		X‡	X†	
			Dondo				TES
		Tete	Moatize				TES
	North	Niassa	Cuamba		X‡	X†	
		Nampula	Mecuburi, Malema, Lalaua and Muecate		X‡	X†	SMC
		Zambézia	Mopeia		X‡	X†	MDA-IVM and TES
		Cabo Delgado	Montepuez				TES

*Year round, all ages.

†Year round, first ANC visit.

‡Rainy and dry season; 2–10 years of age.

ANC, antental care clinics; HFS, health facility survey; MDA-DP, mass drug administration with dihydroartemisinin-piperaquine; MDA-IVM, mass drug administration with ivermectin; PMC, Perennial malaria chemoprevention; React, reactive surveillance; SMC, seasonal malaria chemoprevention; TES, therapeutic efficacy study.

**Figure 2 F2:**
[figure not shown]
Low and medium-to-high transmission study districts targeted in the protocol. ANC, antental care clinics.

Dense sampling will be conducted in the low transmission districts of Magude and Matutuine (Maputo Province), where all the individuals of any age (>6 months old) with clinical symptoms of malaria (defined as axillary temperature ≥37.5°C or history of fever in the preceding 24 hours) and a parasitologically confirmed malaria diagnosis via RDT or microscopy (table 2) will be invited to donate their RDT for molecular analysis (dense sampling).

**Table 2 T2:** Study eligibility criteria

Inclusion criteria	Exclusion criteria
**Low transmission Provinces**	
> 6 months	Any symptoms of severe malaria
Fever (axillary temperature ≥37.5°C) or history of fever in the preceding 24 hours	Negative parasitological test for malaria via RDT or microscopy (except any women at their first ANC visit, who will be recruited before testing for malaria with an RDT)
Positive parasitological test for malaria diagnosis via RDT or microscopy	Unwilling to provide informed, written consent
Household contact of someone with fever/history of fever and *Plasmodium falciparum* positive RDT	History of antimalarial treatment in the last 14 days
OR	
Pregnant women attending first antenatal care visit in Magude district	
AND	
Informed, written consent to participate from participant and/or guardian	
**High transmission Provinces**	
Children aged 2–10 years of age	Any symptoms of severe malaria
Fever (axillary temperature ≥37.5°C) or history of fever in the preceding 24 hours	
Positive parasitological test for malaria diagnosis via RDT* or microscopy	Negative parasitological test for malaria via RDT or microscopy (except any women at their first ANC visit, who will be recruited before testing for malaria with an RDT)
OR	
Pregnant women attending first antenatal care visit	Unwilling to provide informed, written consent
AND	History of antimalarial treatment in the last 14 days
Informed, written consent to participate from participant and/or guardian	

*A second RDT (HRP2-pLDH) will be provided in these locations to support detection of *P. falciparum hrp2* deletions.

ANC, antenatal care; RDT, rapid diagnostic test.

Targeted sampling will be conducted at selected health facilities in the low transmission districts of Boane and Manhiça (Maputo Province), and KaMavota, KaMaxaqueni and Nhamankulu Districts (Maputo City), where a drop of blood will be collected onto filter paper from consenting individuals of any age (>6 months old) with confirmed clinical malaria. In medium-to-high transmission areas, targeted sampling will focus on children aged 2–10 years of age attending selected health facilities with clinical symptoms of malaria and a parasitologically confirmed malaria diagnosis via RDT (table 2). Ten health facilities will be targeted in each district.

Pregnant women attending their first antenatal care visit (any trimester) will be invited to participate both in low (Maputo Province) and high transmission provinces (Inhambane, Gaza, Nampula, Niassa, Manica, Sofala and Zambézia; table 1), irrespectively of malaria clinical symptoms.

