### Enrolment of participants

Dense sampling in Magude and Matutuine districts will be coordinated with district malaria focal points, community health workers (CHW), malaria volunteers (who provide a link between the CHW and the health facility, and assist the CHW in the follow-up of cases and administration of medication) and health facilities. All *P. falciparum* positive RDTs (i.e., SD Bioline Malaria Ag Pf, 05FK50, Abbott) will be stored for molecular analysis. RDTs of *P. falciparum*-confirmed household contacts will also be collected to estimate the rate of within-household transmission. Targeted sampling through health facility-based surveys (HFS) in low and medium-to-high transmission settings will be carried out by one team comprised of one maternal and child health nurse, a laboratory technician or a medical technician. The number of people to be screened in each health facility and the duration of recruitment to achieve the sample size will be dependent on the RDT-positivity rate among people meeting the eligibility criteria. A second test including a non-HRP2 line (StandardQ Malaria Pf/Pan Ag Test, SD Biosensor) will be carried out in HFS during the rainy season and discrepant results suggestive of *pfhrp2/3* deletions will be recorded and further analysed to confirm the deletion. Nurses at the ANC clinics will be in charge of the recruitment of pregnant women at their first visit. Pregnant women will be tested for malaria using a routine RDT and the result will be recorded in a standard questionnaire, together with routine ANC tests. Each enrolled individual will be assigned with a unique identification (UID) number and a barcode.

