### Study outcomes and sample size calculations

The primary endpoints are as follows: (a) prevalence of molecular markers of diagnostic and antimalarial resistance by period, study area and population (use case 1); (b) genetic-relatedness indicators between pairs of samples and populations by period, study area and population (use case 2) and (c) genetic diversity indicators by period, study area and population (use case 3). Sample size per sampling domain (Province) has been estimated considering antimalarial and diagnostic resistance as a primary use case, considering the negligible carriage of molecular markers of artemisinin resistance^5^ and *pfhrp2/3* deletions^6^ in Mozambique, and setting 5% as the warning threshold.^43^ Assuming a 10% of loss of samples or uninterpretable analysis, a sample size of up to 500 per sampling domain would be adequate to: (a) estimate a proportion of 0.05 (markers of drug resistance or *pfhrp2* deletion) with 0.026 absolute precision and 95% confidence and (b) achieve a power of 80% for detecting an increase of genetic marker (resistance or deletion) from 0 ‰ to 5% at a two-sided p-value of 0.01. A flexible and adaptive sampling scheme will be followed, where (a) estimates generated during the first half of the project will inform subsequent sampling schemes and (b) not all the samples collected will be analysed (some of them will be stored as reference materials, for confirmation of findings or future studies on *Plasmodium* biology). The number of pregnant women to be recruited in order to reach the sample number will depend on the parasite rates in the study areas; assuming an overall RDT positivity rate of 25%, we expect we will be needing to recruit a total of 2000 pregnant women per site to get 500 *P*. *falciparum* positive samples, although numbers may differ between sites.

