## Discussion

There is a growing acceptance that genomics can play a critical role in policy and programmatic decisions. With the aim of demonstrating the programmatic application and feasibility of malaria genomic surveillance in Mozambique, we will generate parasite genomic data across varying transmission scenarios for supporting strategic decision-making. First, MMS data will inform drug and diagnostic choices through the monitoring of molecular markers of antimalarial and diagnostic resistance. The emergence of *pfhrp2/3* deletions,^6–8^ resistance to artemisinin^37^ and partner drugs, as well as the resistance to SP used for chemoprevention,^38 46 47^ threatens the global effort to reduce the burden of malaria.^33^ The WHO recommends that countries with reports of *pfhrp2/3* deletions, and neighbouring countries, should conduct representative baseline surveys among suspected malaria cases. If the prevalence of molecular markers of antimarial resistance or deletions causing false negative RDT results reaches the threshold of >5%, then there is need to consider alternative antimalarials and RDTs. Second, the project will help to target the reservoirs sustaining transmission by quantifying parasite importation, identifying sources and characterising local transmission in near-elimination settings.^48 49^ Genomic surveillance and phylogenetic analyses have enabled the near real-time estimation of transmission chains of non-sexually recombining, rapidly evolving pathogens such as Ebola,^50^ influenza^51^ and COVID-19.^52^ However, molecular and analytic advancements are still required to characterise transmission patterns of pathogens such as *P. falciparum* with a sexually recombining stage.^49^ Third, the project will assess the value of *P. falciparum* genetic diversity measures to supplement traditional surveillance for improving stratification, monitoring and impact evaluations in different epidemiological contexts, especially where surveillance data are sparse. This use case still requires development of analytical and interpretative to infer malaria burden^18 20 53–58^ and effectiveness of interventions,^18–23 53 59–61^ as well as validation of sampling frameworks.^4^ Finally, the project will test if parasite populations within pregnant women are representative of the general population and expand the usefulness of this approach to inform genomic surveillance indicators.

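### Outside the dual-tested rainy-season surveys, enrolment on the routine HRP2-based RDT biases pfhrp2/3 deletion prevalence downward, yet endpoint (a) covers those strata against a 5% threshold

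*Protocol article*

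**What the plan says.** **Endpoint and threshold.** Under Study outcomes and sample size calculations, primary endpoint (a) is the "prevalence of molecular markers of diagnostic and antimalarial resistance by period, study area and population". The same section sizes each Province on this use case and sets 5% as the warning level. The Discussion attaches a threshold above 5% to drug-resistance markers and to deletions that produce a false-negative RDT. It also reports WHO advice that countries with reported deletions, and their neighbours, "should conduct representative baseline surveys among suspected malaria cases".

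**Which test is used where.**
- Study design: "During the high transmission (rainy) season, an LDH-based RDT will be added to the standard routine HRP2-based diagnostics to identify potential false negative results".
- Enrolment of participants: "A second test including a non-HRP2 line (StandardQ Malaria Pf/Pan Ag Test, SD Biosensor) will be carried out in HFS during the rainy season". The same sentence adds that discrepant results pointing to a deletion are recorded and followed up for confirmation.
- Dense sampling (Magude and Matutuine): the specimen is the positive routine RDT.
- Children in medium-to-high transmission areas are those "attending selected health facilities with clinical symptoms of malaria and a parasitologically confirmed malaria diagnosis via RDT (table 2"). In the dry season the only RDT described is the routine HRP2-based one.
- Antenatal care (ANC): women are recruited before testing, and targeted sampling takes blood spots from each participant. The ANC target, however, counts RDT-positive samples.

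**Table 2, high transmission provinces.** The inclusion row reads "Positive parasitological test for malaria diagnosis via RDT* or microscopy". Its footnote says "A second RDT (HRP2-pLDH) will be provided in these locations to support detection of" hrp2 deletions and names no season. The exclusion row reads "Negative parasitological test for malaria via RDT or microscopy (except any women at their first ANC visit", and the bracket goes on to explain that these women are recruited before testing.

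**The concern.** A pfhrp2 deletion matters to the programme because it can make an HRP2-based RDT negative. If a positive result on that RDT is the gate into the sample, the infections of interest are the ones most likely to be left out. The loss occurs at enrolment, so no later analysis can recover it.

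The 5% level is meant to inform the choice of RDT. A low figure from a stratum selected on HRP2 positivity could be read as reassurance when it partly reflects the selection. The Analysis plan also foresees comparing genetic metrics between seasons and between pregnant women and community samples. For deletions, a contrast between dual-tested and HRP2-only samples would partly measure which test was used.

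Table 2 adds a separate problem. A child who is HRP2-negative and pLDH-positive meets the footnoted inclusion row and, read literally, the exclusion row too. A field team applying the table as written could drop the cases that the second test is meant to find.

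**Working it through.** **1. The plan's own sample size.** Inputs from Study outcomes and sample size calculations: proportion 0.05, precision 0.026, 95% confidence; power 80% for 0 versus 5% at two-sided 0.01; 10% loss; up to 500 per Province.
- Precision: 1.96² × 0.05 × 0.95 / 0.026² = 270; 270 / 0.9 = 300.
- Power, two-group normal approximation without continuity correction: 227 per group, 454 in total; 454 / 0.9 = 505.

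The stated 500 is therefore reproduced as a two-group total for the power target, and it more than covers the precision target. Neither calculation allows for selection on HRP2 positivity.

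**2. Effect of selection.** Let p be the true deletion prevalence among infections, f the share of deleted infections that are HRP2-RDT negative, and Se the RDT's sensitivity for non-deleted infections. The protocol gives neither f nor Se, so both are assumptions. Among HRP2-RDT-positive infections:

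observed = p(1 − f) / [p(1 − f) + (1 − p)Se]

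With p = 0.05:

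| f | Se = 1 | Se = 0.95 |
|---|---|---|
| 0.5 | 0.025 / 0.975 = 2.6% | 0.025 / 0.9275 = 2.7% |
| 0.8 | 0.010 / 0.960 = 1.0% | 0.010 / 0.9125 = 1.1% |
| 0.9 | 0.005 / 0.955 = 0.5% | 0.005 / 0.9075 = 0.55% |
| 1.0 | 0% | 0% |

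The result is sensitive to f and hardly moves with Se.

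**3. True prevalence needed before such a stratum shows 5%** (Se = 1): 0.05 / [0.95(1 − f) + 0.05].
- f = 0.5: 0.05 / 0.525 = 9.5%
- f = 0.8: 0.05 / 0.24 = 21%
- f = 0.9: 0.05 / 0.145 = 35% (rounded up from 34.5%)

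**4. Power against zero at two-sided 0.01, true prevalence 5%, Se = 1.** The 500 can be read as per group (500 × 0.9 = 450 evaluable) or as the two-group total (225 evaluable per group).

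| Evaluable per group | No selection | f = 0.5 | f = 0.8 | f = 0.9 |
|---|---|---|---|---|
| 450 | 98.8% | 80% | 34% | 15% |
| 225 | 80% | 44% | 15% | 7% |

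**5. Pooling seasons.** Suppose half of a Province's samples come from a rainy-season survey that keeps discordant cases and half from HRP2-only sampling. The pooled estimate is then 0.5 × 5% + 0.5 × 2.6% = 3.8% at f = 0.5, falling to 0.5 × 5% = 2.5% at f = 1.

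**6. The threshold quantity itself.** The Discussion ties the threshold to deletions that cause a false-negative RDT. An infection with a false-negative HRP2 result cannot be in a sample selected on a positive one. Where the HRP2-based RDT is the only gate, that quantity is zero by construction, whatever f is.

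**7. Texts that do not agree.**
- Exclusion row: a negative RDT excludes. Inclusion row with footnote: a positive second RDT qualifies. Enrolment of participants: discrepant results are kept for confirmation.
- Footnote: no season. Study design and Enrolment of participants: rainy season only.
- Table 2: RDT or microscopy. Text on children in medium-to-high areas: RDT only.

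**The case against.** Three stronger readings are tempting, and the protocol does not support them.

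- **Table 2 simply excludes HRP2-negative/pLDH-positive children.** The exclusion row reads more naturally as the complement of the inclusion row, whose footnote points to the second RDT. Taken literally, it would also drop a child who is RDT-positive and microscopy-negative. Study design and Enrolment of participants show an intention to keep discordant cases. What stands is a conflict to reconcile, not a settled exclusion.
- **Every sample outside the rainy-season survey is HRP2-positive.** Table 2 also admits microscopy-positive cases, and ANC women give blood spots whatever their RDT result. The ANC figure of 2000 women for 500 positives (500 / 0.25) is a recruitment forecast, not an enrolment rule. Selection affects ANC only if just the RDT-positive women are sequenced.
- **The deletion endpoint is driven to near zero.** That needs a high f. The Discussion says that polyclonal infections are frequent at all transmission levels. A deleted clone carried with an intact one may still give a positive RDT, which lowers f. At f = 0.5 the observed figure is 2.6%.

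It is also fair to say that the phrase on period, area and population is the same for all three primary endpoints, that a full protocol or SAP may define the deletion denominator, and that the WHO advice on suspected cases does not define this study's population. None of this removes the bias in dense and dry-season samples, because it arises from who is enrolled.

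**Conclusion.** The point holds for dense sampling and the dry-season health facility surveys. Enrolment there rests essentially on the routine HRP2-based RDT, so deletion prevalence is biased downward, while endpoint (a) as worded covers these strata against a 5% threshold. The direction follows from the protocol's own account of why the LDH-based test is added. The size does not: a true 5% would appear as anything from 2.6% down to 0% for f between 0.5 and 1, given full RDT sensitivity for non-deleted infections, and f is an assumption. Microscopy-confirmed cases, where they are actually enrolled, would soften the bias.

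The Table 2 wording is a contradiction that could cost discordant cases even in the dual-tested survey. Prevalence of drug-resistance markers is not called into question by this argument.

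**What to change.** 1. **Reconcile Table 2 with Study design and Enrolment of participants.** Word the exclusion as negative on every malaria test performed, so that an HRP2-negative/pLDH-positive child is clearly eligible. Align the footnote with the text on season, and the table with the text on microscopy.
2. **Base the 5% threshold reading for deletions on dual-tested rainy-season health facility participants.** The denominator is all P. falciparum infections positive on either test.
3. **Label the other strata.** Report deletion estimates from dense and dry-season samples as being among HRP2-RDT-positive infections. Do the same for ANC samples if only RDT-positive women are sequenced. Do not read these estimates against the threshold, and do not contrast them by season or population with dual-tested samples.

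The second test is already planned, so the cost is wording in the eligibility table and the endpoint definition. The drawback is that the threshold reading is available for fewer settings.
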